#### 5.4.3 Subgroups

Stratified analysis will be done for three pair-wise comparisons (RUTF vs. control, MNP vs. control, RUTF vs. MNP (as described in 5.4.1) according to the following subgroups (measured at baseline):

- age (binary: <36 months, ≥36 months)
- gender
- current breastfeeding practices (no, partial breast feeding)
- underlying illnesses (only malaria, only diarrhoea, only LRTI, 2 or more diseases)
- socio-economic status (low, moderate, high)
- food availability (binary or in tertile)
- length of illness before visiting MSF clinic (binary or in tertile)
- recruitment period (binary or in tertile)
- malnourishment status(non-acutely malnourished or moderately acutely malnourished)

To assess the presence of effect modification for these factors, models with interaction terms will be analysed.

#### 5.4.4 Missing endpoint data

The amount, pattern, timing and distribution of missing data of the primary endpoint will be checked by a person blinded to treatment allocation. A decision based upon the result of this check will be made as to whether and how imputation of missing primary endpoint data will be performed as a sensitivity analysis on the ITT population for the analysis in 5.4.1.

#### 5.4.5 Per protocol analysis

The analysis as described in 5.4.1 will be repeated for the per protocol population.

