## **4.2 Per protocol population**

The per protocol population (PP) includes all patients of the ITT population which were treated following the specifications of the study protocol without major protocol deviations. Excluded from the per protocol population will be patients that meet at least one of the following criteria:

- Violation of one of the following exclusion criteria: exclusive breastfeeding, hospitalisation for serious complicated illness (e.g. chronic illness).
- Not treated according to the allocated intervention group
  - For the RUTF group (for each 14-day supplementation period)
    - less than 12 days of supplement taken by the child
    - less than 12 sachets consumed by the child
    - less than 12 empty sachet counted
  - For the MNP group (for each 14-day supplementation period)
    - less than 24 days of supplement taken by the child
    - less than 24 sachets consumed by the child
    - less than 24 empty sachet counted
  - For all three groups (RUTF, MNP, control): having taken RUTF or MNP outside the study allocation (e.g. as part of measles treatment)
- Patient misses 3 or more scheduled visits
- Patient misses 2 or more consecutive scheduled visits
- Patient misses the last scheduled visit (6 months visit)
- Participation in other feeding programmes

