### 5.3 Primary analysis of primary endpoint

The primary endpoint is “negative nutritional outcome” of a child within the 6 months follow-up period. The incidence rate (in formulae below referred to simply as ‘rate’) of “negative nutritional outcome” will be computed as the number of events divided by total observed person-time in each treatment group. As an “event” the first time a child reaches a negative nutritional outcome will be used. The primary analysis of the primary endpoint will be performed on the intention to treat population with no imputation of missing data.

In the primary analysis, RUTF will be compared to the control group

The hypotheses in this step are

$$H_0: \text{rate}_{\text{RUTF}} = \text{rate}_{\text{Control}}$$

vs.

$$H_1: \text{rate}_{\text{RUTF}} \neq \text{rate}_{\text{Control}}$$

where  $\text{rate}_{\text{RUTF}}$  = rate of “negative nutritional outcome” in the children in the RUTF group, and  $\text{rate}_{\text{Control}}$  = rate of “negative nutritional outcome” in the children in the control group.

The comparison of rates among the two treatment groups (RUTF vs. control) will be performed by a Poisson regression model, adjusted for nutritional status at enrolment (fixed effect) and will be performed within one model including the three intervention groups with contrasts for each two-group comparison. The result will be presented as rates for each intervention group, and a rate ratio for the pair-wise comparison (each with 95% confidence intervals). Tests will be two-sided with a significance level of 0.05.

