### 5.4 Secondary analysis of the primary endpoint

#### 5.4.1 Treatment group comparisons

Although the study is primarily powered for the comparison between the RUTF and control group the other groups will be compared as well, keeping in mind that the sample size might not be large enough to obtain significant results.

Since there are three interventional groups to be compared, a hierarchical test procedure will be used to account for multiplicity.

i) In a first (primary) step, RUTF will be compared to the control group which is described above as analysis of primary outcome

If the RUTF group is not significantly different at a 0.05 level (two-sided test), the hierarchical procedure is stopped (all following analyses will be considered explorative). If the RUTF group is significantly different at a 0.05 level, the hierarchical procedure is continued with step 2.

ii) In the second step, MNP will be compared to the control group

The hypotheses in this step are

$$H_0: \text{rate}_{\text{MNP}} = \text{rate}_{\text{Control}}$$

vs.

$$H_1: \text{rate}_{\text{MNP}} \neq \text{rate}_{\text{Control}}$$

where  $\text{rate}_{\text{MNP}}$  = rate of “negative nutritional outcome” in the children in the MNP group, and  $\text{rate}_{\text{Control}}$  = rate of “negative nutritional outcome” in the children in the control group.

If the treatment factor is not significant at a 0.05 level (two-sided test), the hierarchical procedure is stopped (all following analyses will be considered explorative). If the treatment factor is significant at a 0.05 level, the hierarchical procedure is continued with step iii).

iii) In the third step, RUTF will be compared to MNP (non-inferiority test).

The hypotheses in this step are

$$H_0: \text{rate}_{\text{RUTF}} - \text{rate}_{\text{MNP}} > -\delta$$

vs.

$$H_1: \text{rate}_{\text{RUTF}} - \text{rate}_{\text{MNP}} \leq -\delta$$

where  $\text{rate}_{\text{RUTF}}$ =rate of “negative nutritional outcome” in the children in the RUTF group,  $\text{rate}_{\text{MNP}}$ =rate of “negative nutritional outcome” in the children in the MNP group, and  $\delta$ =inferiority margin.

As non-inferiority margin, a  $\delta$  of 2% (absolute value) will be used (i.e. allowing a slightly worse result in the MNP compared to the RUTF group). The third step will be tested at a 0.025 level (one-sided test), by a one-sided 97.5% confidence interval of the difference in rates between the RUTF and the MNP group.

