The general problem of assay sensitivity in non-inferiority comparisons can be addressed in this study by the 3-arm design including a control group receiving no nutritional supplementation. Thus, superiority of the two nutritional interventions (RUTF and MNP) versus no intervention can be evaluated prior to the non-inferiority comparison.

These step-wise comparisons of rates among treatment groups will be performed by the same Poisson regression model, adjusted for nutritional status at enrolment (fixed effect) as described above, i.e. performed within one model including the three intervention groups with contrasts for each two-group comparison. The results will be presented as rates for each intervention group, and rate ratios for the pair-wise comparison (each with 95% confidence intervals).

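### Step iii (MNP versus RUTF non-inferiority) is by implication decided on ITT, and the per-protocol repeat has no part in the decision, so dilution can raise the false non-inferiority rate

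*SAP*

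**What the plan says.** - **Step iii.** SAP section 5.4.1 tests RUTF against MNP at a one-sided level of 0.025, "by a one-sided 97.5% confidence interval of the difference in rates between the RUTF and the MNP group". The margin is 2% in absolute terms, and the stated intent is to let MNP be slightly worse. Step iii is confirmatory only if RUTF and then MNP have each differed from control at two-sided 0.05.
- **Analysis set.** Section 5.3, on RUTF versus control, says: "The primary analysis of the primary endpoint will be performed on the intention to treat population with no imputation of missing data". Section 5.4.1 names no set for steps ii and iii, but uses the same Poisson model. Section 5.4.4 plans possible imputation "as a sensitivity analysis on the ITT population for the analysis in 5.4.1". ITT is therefore implied for step iii, not stated.
- **Per-protocol analysis.** Section 5.4.5 reads in full: "The analysis as described in 5.4.1 will be repeated for the per protocol population". It does not say whether the two results must agree, or which one governs.
- **Departures foreseen.** Section 4.2 removes children with too few days or sachets from the per-protocol set. In all three groups it also removes those "having taken RUTF or MNP outside the study allocation". Section 4.1 keeps all of them in ITT.
- **Safeguard offered.** On assay sensitivity, section 5.4.1 notes that "superiority of the two nutritional interventions (RUTF and MNP) versus no intervention can be evaluated prior to the non-inferiority comparison".

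**The concern.** In steps i and ii dilution works against the claim, so ITT is the cautious set. In step iii the claim is that two arms are close, so whatever makes them alike helps it. Children who miss doses or take a supplement outside their allocation stay in ITT, and courses repeated over six months give many occasions for both.

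MNP could thus be called non-inferior because the products were taken poorly or mixed, while the per-protocol analysis points the other way, and the SAP would not say how to read the conflict. If ITT is not accepted as the implied set, the choice between sets is open until both results are known.

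**Working it through.** **The plan's own figure.** A one-sided 97.5% limit corresponds to 1 − Φ(1.960) = 0.025, which matches the stated level. The SAP gives no sample size, event rates or adherence, so everything below rests on assumptions.

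**Inputs**
- From the SAP: margin δ = 0.02 and one-sided level 0.025. No person-time unit is given, so I read the margin as 2 points over the six months of follow-up.
- Assumed: n = 700 per arm; rates of 20% (control), 10% (RUTF) and 12% (MNP) when taken as allocated, so the true MNP − RUTF difference sits exactly at the margin; share f of children departing from allocation of 10, 20 or 30%.

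**Formula, step iii alone.** Let d be the difference MNP − RUTF that ITT sees. Under the stated intent, non-inferiority is concluded if the upper limit for MNP − RUTF is below δ:

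false rate = Φ((δ − d)/SE − 1.960), with SE = √((rate RUTF + rate MNP)/n).

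At f = 0 this gives Φ(−1.960) = 2.5%.

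**Worked at f = 20%**
- *Cross-over in both directions.* RUTF = 0.8×0.10 + 0.2×0.12 = 0.104; MNP = 0.8×0.12 + 0.2×0.10 = 0.116; d = 0.012. SE = √(0.220/700) = 0.01773. Φ(0.451 − 1.960) = 6.6%.
- *MNP children taking RUTF, not the reverse.* RUTF = 0.100; MNP = 0.116; d = 0.016. SE = √(0.216/700) = 0.01757. Φ(0.228 − 1.960) = 4.2%.
- *Missed doses equally in both arms (the child reverts to the control rate).* RUTF = 0.120; MNP = 0.136; d = 0.016. SE = √(0.256/700) = 0.01912. Φ(0.209 − 1.960) = 4.0%.
- *Missed doses in RUTF only.* RUTF = MNP = 0.120; d = 0. SE = √(0.240/700) = 0.01852. Φ(1.080 − 1.960) = 19.0%.
- *Missed doses in MNP only.* RUTF = 0.100; MNP = 0.136; d = 0.036. SE = √(0.236/700) = 0.01836. Φ(−0.871 − 1.960) = 0.2%.

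**Adding the superiority steps.** Poisson simulation gives the probability that both supplements beat control and non-inferiority is then concluded falsely.

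| Pattern (n = 700; 20/10/12%) | Step iii alone, f = 10/20/30% | After steps i and ii |
|---|---|---|
| Cross-over, both directions | 4.1 / 6.6 / 10.0% | 4.1 / 6.5 / 9.7% |
| MNP children taking RUTF only | 3.2 / 4.2 / 5.3% | not given |
| Equal missed doses | 3.2 / 4.0 / 4.9% | 3.0 / 3.3 / 3.1% |
| Missed doses in RUTF only | 8.0 / 19.0 / 35.5% | not given |
| Missed doses in MNP only | 0.8 / 0.2 / 0.06% | not given |

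**Other assumed settings, after steps i and ii, at f = 20%**
- n = 2000, 20/10/12%: 11.6% for cross-over and 5.5% for equal missed doses.
- n = 700, 20/15/17%: under 1% for cross-over and 0.3% for equal missed doses.
- n = 300, 20/10/12%: 1.0% for equal missed doses.
- n = 1000, 20/15/17%: 0.8% with full adherence and 2.1% with cross-over. Dilution more than doubles the rate here, but it stays under 2.5%.

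**The case against.** Four objections have weight.

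- **ITT is valid for the effect of assignment.** This stands. If step iii asks what happens when children are assigned to one product or the other, with whatever adherence follows, the 2.5% holds. The SAP leaves the target unclear: section 1 speaks of effectiveness, while section 1.2 uses efficacy in the objective that covers this comparison.
- **The superiority steps protect step iii.** This stands in part. They hold equal missed doses near 3% in the main scenario, and the overall rate below 2.5% in several settings where they are hard to pass. They do little against cross-over, because both arms still beat control.
- **The direction is unknown, and section 4.2 does not describe children exchanging products.** This also stands. Missed doses mainly in MNP make a false claim less likely. The listed departure is supplement from outside the allocation, with measles treatment as its example. More RUTF for a RUTF child is not cross-over, so the two-way figures are the upper part of the range. RUTF reaching MNP children alone gives 3.2-5.3% for step iii by itself.
- **The per-protocol set is no unbiased arbiter.** It is selected after randomisation, partly on visit attendance. That argues against letting it replace ITT, but not against requiring it to agree.

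A reader might infer that deciding on ITT necessarily pushes the error above 2.5%, or that the SAP expressly assigns step iii to ITT. The documents support neither: the set is inferred, and the size and direction depend on adherence and rates that the SAP does not give.

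**Conclusion.** The gap is real, and a correction should be made. The SAP gives the per-protocol result no role in a confirmatory non-inferiority decision and does not say how discordant results are read. The false non-inferiority rate, relative to the difference between the supplements taken as allocated, can exceed 2.5%. In the main assumed scenario (700 per arm, 20/10/12%) it is about 3% for equal missed doses and 4-10% for 10-30% two-way cross-over after the superiority steps. Other assumed settings run from below 1% to 11.6%. Steps i and ii are unaffected.

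Two faults in the SAP limit what can be concluded now:
- Section 4.2 asks MNP children for at least 24 days of supplement in each 14-day period. Read literally, this empties the MNP per-protocol arm.
- The step iii hypotheses run against their stated intent. For an unfavourable outcome, the alternative as written (RUTF − MNP ≤ −δ) says that MNP is worse by at least the margin. A claim that MNP is non-inferior follows only from the accompanying explanation.

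**What to change.** First reconcile the MNP per-protocol criterion with the 14-day period to which it applies, and the direction of the step iii hypotheses with the stated intent. Until then a rule that uses both sets cannot be met.

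Then add to section 5.4.1, step iii, with a cross-reference in section 5.4.5:

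*Step iii is analysed in the ITT and the per-protocol population. Non-inferiority of MNP to RUTF is concluded only if the confidence limit lies within the margin in both; otherwise it is not concluded. Steps i and ii are decided on ITT.*

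Under this rule the false rate cannot exceed the smaller of the two sets' rates, which is at most 2.5% if the per-protocol comparison is itself unbiased. That condition is not guaranteed, so the per-protocol set is an added safeguard beside ITT and not a substitute.

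The cost is a few sentences, since the per-protocol analysis is already planned, the two reconciliations, and some loss of power in step iii.

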## **5.5 Analysis of secondary endpoints**

All secondary endpoints (as defined in section 3.2) will be compared between the three treatment groups as described in 5.4.1 (p-values will be considered explorative) for the ITT and the PP populations. In addition to the Poisson regression model, logistic regression model, analysis of variance (ANOVA), analysis of covariance (ANCOVA), Cox proportional hazard model, and non-parametric analysis of variance will be used, according to the type of endpoint. In case of relevant differences in baseline characteristics additional adjustment(s) for these factors may be performed. Stratified analyses are planned for secondary endpoints regarding weight and weight change with respect to age, gender, and breast feeding.

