### **1.2 Secondary objectives**

Secondary objectives include the following.

- Incidence of malnutrition

Determine the efficacy of 14 days MNP supplementation versus a control group and RUTF versus MNP on the incidence of acute malnutrition during 6 months follow-up,

- Frequency of morbidity

Determine the effect of 14 days supplementation on the frequency of morbidity (3 study diseases) during 6 months follow-up, comparing both intervention groups to the control group and comparing RUTF to MNP)

- Weight changes immediately after intervention period, measured at day-14 and day-28

Measure mean weight change (total change and rate (grams/kg/day) of change), comparing both intervention groups separately (RUTF and MNP) to the control group

Determine frequency of 'no weight gain and/or weight loss', comparing both intervention groups separately (RUTF and MNP) to the control group

Assess if provision of 14 days of RUTF or MNP supplement promotes a sustained weight gain, measured after 28-days of follow-up, comparing both intervention groups separately (RUTF and MNP) to the control group

- Evaluation of several subgroup to assess potential effect modifiers.

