## **2 Study design**

This is a partially blinded randomized controlled trial with three study groups. Children 6 to 59 months of age presenting at the OPD in Goronyo and diagnosed with one or more of the three study diseases (malaria, diarrhoea and LRTI) are eligible for the study.

Children participating in this study will be randomised to one of 3 study groups to:

- A) Receive 14 days of RUTF supplementation with standard care and treatment or
- B) Receive 14 days MNP supplementation with standard care and treatment or
- C) Be included in a control group receiving standard care and treatment but not receiving nutritional supplementation (control group)

Individual follow-up will be 6 months. During this time, children in the RUTF or MNP group will receive 14 days nutritional supplement every time diagnosed with at least one of the three study diseases, not exceeding more than 14 days supplementation in any 28 day period.

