#### **3.2 Secondary endpoints**

Secondary endpoints include

- Number of NNO’s per study group in a period of 6 months
- Time to NNO
- Number of new events of a study disease in 6 months
- Weight change at 14 days and 28 days after study inclusion, and at end of study period
- Rate of weight change (grams/kg/day) at 14 days and 28 days after study inclusion, and at end of study period
- Proportion of children not gaining weight (including losing weight), measured at day-14 and day-28 after study inclusion.
- Proportion of children developing bilateral oedema, overall and per month
- Proportion of moderate acutely malnourished children improving to a non acutely malnourished state, overall and per month
- Mortality: overall mortality
- Morbidity, including the three study diseases (proportion of children with newly diagnosed diseases), overall and per month
- Proportion of children with a reported cough at clinical visit, overall and per month
- Proportion appetite categories
- Proportion and time pattern of children who were breast-fed at baseline and stopped being breast-fed during the study

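### Section 5.5 defaults the repeated study-disease count to a Poisson model with no provision for overdispersion, so its exploratory rate-ratio intervals may be too narrow

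*SAP*

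**What the plan says.** SAP section 1.2 makes morbidity a secondary objective: "Determine the effect of 14 days supplementation on the frequency of morbidity (3 study diseases) during 6 months follow-up". Section 3.2 turns this into the endpoint "Number of new events of a study disease in 6 months". It also lists the number of negative nutritional outcomes (NNOs) "per study group in a period of 6 months".

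Section 2 expects repeat illness. Children in the two supplement groups "will receive 14 days nutritional supplement every time diagnosed with at least one of the three study diseases", and "Individual follow-up will be 6 months".

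Section 5.5 states that all secondary endpoints "will be compared between the three treatment groups as described in 5.4.1 (p-values will be considered explorative"). Section 5.4.1 is a single Poisson regression with the three groups and nutritional status at enrolment as a fixed effect, reported as rates and rate ratios with 95% confidence intervals. Section 5.5 then adds other methods: "In addition to the Poisson regression model, logistic regression model, analysis of variance (ANOVA), analysis of covariance (ANCOVA), Cox proportional hazard model" and, closing the same sentence, "non-parametric analysis of variance will be used, according to the type of endpoint".

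The SAP does not mention overdispersion, a scale parameter, robust or clustered variance, a negative binomial model or a child-level random effect.

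**The concern.** In the primary analysis (section 5.3) a child contributes at most one event, so recurrence within a child does not arise. Section 5.5 carries the same model over to a count where it does.

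A Poisson model with its usual model-based standard errors requires that children in the same arm, with the same nutritional status and follow-up, share one underlying rate, so that the variance of the count equals its mean. Section 5.4.3 lists age, breastfeeding, underlying illness, socio-economic status and food availability as subgroup factors. If any of these, or anything unmeasured, affects illness risk, the variance exceeds the mean. The further adjustments in sections 5.4.2 and 5.5 do not settle this, because they are triggered by baseline differences between arms, not by variation between children within arms.

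At stake is the precision claimed for the morbidity comparison. Reducing the incidence of the three diseases is part of the study aim in section 1. If standard errors from this model were also used in the pooled analyses of section 5.7, any understatement would pass into them.

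**Working it through.** **Inputs from the SAP.** Two-sided level 0.05 and 95% intervals (section 5.3); Poisson model with one covariate (sections 5.3 and 5.4.1); 6 months of follow-up (section 2). The SAP gives no episode rate, dispersion or sample size.

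**Assumed input.** φ = variance/mean of the per-child count. If children's rates vary as a gamma distribution with squared coefficient of variation k around a mean count μ, then φ = 1 + k × μ.

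**Formulas.** The model-based Poisson standard error is too small by the factor 1/√φ. Hence:

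- actual type I error = 2 × [1 − Φ(1.96/√φ)]
- actual coverage of a nominal 95% interval = 2 × Φ(1.96/√φ) − 1
- interval width relative to the correct width = 1/√φ

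**The plan's own figure.** φ = 1 gives 2 × [1 − Φ(1.96)] = 0.05, the stated level.

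**Range of assumed φ.**

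| φ | 1.96/√φ | Type I error | Coverage of 95% CI | Relative width |
|---|---|---|---|---|
| 1.0 | 1.96 | 5.0% | 95.0% | 1.00 |
| 1.2 | 1.79 | 7.4% | 92.6% | 0.91 |
| 1.5 | 1.60 | 11.0% | 89.1% | 0.82 |
| 2.0 | 1.39 | 16.6% | 83.4% | 0.71 |
| 3.0 | 1.13 | 25.8% | 74.2% | 0.58 |

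**What could produce such values.** All of these are assumptions. A mean of 1 episode with k = 0.5 gives φ = 1 + 0.5 × 1 = 1.5. A mean of 2 with k = 0.5 gives φ = 2, and with k = 1 gives φ = 3.

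**Simulation check.** 10,000 trials per setting, an assumed 500 children per arm, no true effect, no covariate:

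| μ, k | φ | Plain Poisson | Per-child robust variance |
|---|---|---|---|
| 2, 0 | 1.0 | 4.9% | 4.9% |
| 1, 0.5 | 1.5 | 10.7% | 5.3% |
| 2, 0.5 | 2.0 | 16.2% | 4.7% |
| 2, 1 | 3.0 | 25.7% | 5.2% |

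The formula is confirmed, and the robust variance restores the nominal level.

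**NNO count.** At an assumed mean of 0.2 per child, k = 0.2, 0.4 and 0.8 give φ = 1.04, 1.08 and 1.16, and type I error of about 5.5%, 5.9% and 6.9%. At a low mean the effect is small unless k is much larger.

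**The case against.** - **Other listed methods avoid the problem.** A reader who stops before the end of the method list might infer that no listed method escapes the Poisson variance. That is not so. A rank-based comparison of per-child counts does not use it, and ANOVA estimates the variance from the data. This stands. But the SAP assigns neither to the study-disease count, and neither yields the person-time rate ratio that section 5.4.1 reports.
- **The SAP does not rule out a correction.** It names a regression family and a covariate, not a variance estimator. A reader might infer a decision to ignore overdispersion, but the text shows only silence. This stands too, and makes the point a gap in specification. Because section 5.5 defaults to 5.4.1, Poisson remains the natural reading for a count.
- **Secondary p-values are exploratory.** A reader might infer that the trial's false-positive rate is compromised. It is not: section 5.5 labels these p-values exploratory, and section 5.3 counts only the first NNO per child. The label does not widen an interval that is too narrow, however.
- **The size is assumed.** This is correct. That illness varies between children is plausible, but its extent cannot be read from the SAP, and φ = 1 gives no error.
- **The NNO count may not be recurrent.** Section 3.2 words it per study group and does not clearly say that repeats within a child are counted. The illness figures should not be transferred to it.

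**Conclusion.** The point holds as a limited gap. For the number of new study-disease events, the SAP defaults to a Poisson model without provision for between-child variation beyond nutritional status at enrolment. Whenever children differ further in illness risk, the model-based intervals for the rate ratios will be too narrow and the exploratory p-values too small.

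The size depends wholly on an assumed dispersion. It runs from no error at φ = 1 to about 26% false positives and 74% coverage at φ = 3; modest inflation of 1.2 gives about 7% and 93%. The documents do not support saying that any confirmatory conclusion is affected, that every listed method fails, or that the NNO count is affected to the same degree.

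**What to change.** Add a sentence to section 5.5 for the number of study-disease events. It should specify one of two models, chosen before the data are seen:

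- a negative binomial regression with log person-time as offset, adjusted for nutritional status at enrolment; or
- the Poisson regression of section 5.4.1 with robust (sandwich) variance clustered on the child.

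State in section 3.2 whether repeat NNOs within a child are counted. If they are, apply the same model to that count, where the effect is likely to be smaller.

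Both options are available in SAS and Stata, which section 6 already names. The cost is one or two sentences in the SAP and a model option, and wider intervals if counts prove overdispersed. If they do not, little precision is lost. The primary analysis needs no change on this ground.

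### End-of-study weight change, labelled ITT, would in practice compare only children with a 6-month weight, because SAP 5.5 names no longitudinal model and no rule covers missing weights

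*SAP*

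**What the plan says.** SAP 3.2 defines the weight endpoints visit by visit: "Weight change at 14 days and 28 days after study inclusion, and at end of study period", and likewise "Rate of weight change (grams/kg/day) at 14 days and 28 days after study inclusion, and at end of study period".

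SAP 5.5 compares all secondary endpoints between the three arms, with "p-values will be considered explorative) for the ITT and the PP populations". Besides Poisson regression, it states that "logistic regression model, analysis of variance (ANOVA), analysis of covariance (ANCOVA), Cox proportional hazard model, and non-parametric analysis of variance will be used", the choice being made "according to the type of endpoint". No mixed model, GEE or other repeated-measures method is named.

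On missing data, SAP 5.3 runs the primary analysis on the "intention to treat population with no imputation of missing data". SAP 5.4.4 leaves open "whether and how imputation of missing primary endpoint data will be performed as a sensitivity analysis on the ITT population". Neither section says anything about missing weights.

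Three other places bear on the point:
- SAP 4.2 excludes a child who misses the 6-month visit from the PP population.
- SAP 4.3 counts a child as having completed the study if at least the first and the 6-month visits were attended.
- SAP 5.1 promises numbers and reasons for drop-out and loss to follow-up and, if possible, a comparison of respondents with non-respondents.

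**The concern.** An ANOVA or ANCOVA of change to 6 months needs a baseline weight and a 6-month weight. A child weighed at day 14 and day 28 but not at 6 months contributes nothing to it. The set analysed is then essentially the completers of 4.3, although the table would be headed ITT. The PP analysis is no cross-check, because 4.2 removes the same children.

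What is at stake is the end-of-study weight estimate. Suppose children who gained poorly in the first 28 days are more likely to be lost, and more of them are lost from control than from a supplement arm. The remaining controls then look better than the control arm as a whole, and the supplement effect is understated. If loss runs the other way, the effect is overstated. The early weights that would carry information about this loss are already collected, but the listed methods do not use them.

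**Working it through.** **Reading the sections together.** Section 3.2 gives three separate time points. Section 5.5 picks the model by endpoint type, and for a continuous outcome its list offers only ANOVA, ANCOVA and non-parametric ANOVA. Section 5.4.4 confines imputation to the primary endpoint. The analysis of 6-month change therefore falls to children with a 6-month weight. Classical repeated-measures ANOVA is not expressly excluded, but it also drops a child with an incomplete series.

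**No figure to reproduce.** The SAP states no SD, sample size, effect or loss for weight change. Every input below is assumed.

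**Illustration 1: loss fixed per arm.**
- Day-28 and 6-month weight change are bivariate normal with SD 1 and correlation ρ = 0.6.
- After day 28, the log-odds of loss fall by s per SD of day-28 change, with s = 0.5 or 1.0 in both arms. The intercept is set so that each arm has its stated loss.
- Let m(p, s) be the mean standardised day-28 deviation, from the arm's own mean, among children still observed when a proportion p is lost.
- Bias in the 6-month difference (RUTF minus control) = ρ × [m(p_RUTF, s) − m(p_control, s)].

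Numerical integration gives:

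| Loss p | m at s = 0.5 | m at s = 1.0 |
|---|---|---|
| 10% | 0.0488 | 0.0908 |
| 15% | 0.0726 | 0.1326 |
| 20% | 0.0962 | 0.1732 |

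The biases follow:
- 15% control v 10% RUTF: 0.6 × (0.0488 − 0.0726) = −0.014 SD; 0.6 × (0.0908 − 0.1326) = −0.025 SD.
- 20% v 10%: 0.6 × (0.0488 − 0.0962) = −0.028 SD; 0.6 × (0.0908 − 0.1732) = −0.049 SD (−0.0495 before rounding m, so about 0.050).
- Equal loss, same s: the two m terms cancel and the bias is zero.

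The true effect does not enter the formula. As a percentage, the same bias therefore depends on the effect assumed. At 15% v 10% it is 7.1% to 12.5% of a 0.20 SD effect but 3.6% to 6.3% of a 0.40 SD effect. At 20% v 10% it is 14.2% to 24.7% and 7.1% to 12.4%. With smaller loss, 5% v 3%, it is 2.9% to 5.5% of a 0.20 SD effect.

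**Illustration 2: the treatment effect itself drives the loss.** This was simulated with 200,000 children per arm. The true differences were 0.4, 0.4 and 0.2 SD at day 14, day 28 and month 6. The correlations were 0.8 (day 14 with day 28), 0.5 (day 14 with month 6) and 0.6 (day 28 with month 6). The loss model was common to both arms, with base loss of 5% to 30%. The true month-6 difference is 0.20 SD.

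| Slope on day-28 change | Children with a 6-month weight only | Estimate using earlier weights |
|---|---|---|
| 0 | 0.198 to 0.204 | 0.196 to 0.203 |
| 0.5 | 0.184 to 0.195 | 0.196 to 0.200 |
| 1.0 | 0.165 to 0.189 | 0.198 to 0.204 |

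Using the earlier weights recovers the truth to within simulation error, because loss in this set-up depends only on an observed value.

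**The case against.** The best case against is that this is a preference for another method. ANCOVA on available data is conventional for an exploratory secondary endpoint, and it is unbiased if loss is unrelated to weight. Section 5.5 assigns no model to weight change by name and does not say that each visit is analysed alone. Section 1.2 frames the weight objective around day 14 and day 28, so end-of-study weight change appears only in the endpoint list. Section 5.1 would bring weight-related or uneven loss into view. Nothing in the SAP shows that loss will differ by arm or depend on weight.

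Much of this stands. The single-visit analysis is inferred from 3.2 and 5.5 together, not stated. Uneven loss is an assumption; that controls have less reason to return is conjecture. The comparison in 5.1 is a partial safeguard, although it reports selective loss without correcting for it and is promised only if possible. What the objection does not remove is that no listed method for a continuous endpoint uses the earlier weights of a child lost later, that no rule covers missing weights, and that an exploratory p-value does not remove bias from the estimate beside it.

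A reader might also infer that all three weight time points are compromised. The documents do not support that. A child lost before day 14 has no post-baseline weight for any model to use, and no bias has been shown for day 14 or day 28. Nor does the point reach the primary result: section 5.3 analyses first events over observed person-time.

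**Conclusion.** The point holds for end-of-study weight change and the corresponding rate, as a low-severity matter. As written, the comparison labelled ITT would in practice be one among children with a 6-month weight, and the PP analysis shares that restriction.

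Bias needs loss that depends on early weight change and also differs by arm, whether for outside reasons or because treatment changes early weight. Under the first set of assumptions its size is about 0.014 to 0.025 SD at 15% v 10% loss and 0.028 to 0.050 SD at 20% v 10%. It is zero at equal loss with the same dependence in both arms. These are illustrations, not predictions, since the SAP gives no loss figures. It would be wrong to read a fixed percentage loss of effect into them: large percentages come from assuming a small true effect.

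**What to change.** In SAP 5.5, state that weight change in the ITT population is analysed by a mixed model for repeated measures on all observed post-baseline weights. The terms would be arm, visit, arm-by-visit, baseline weight, baseline weight-by-visit and nutritional status at enrolment. Take the end-of-study contrast from this model, and the day-14 and day-28 contrasts as well. Keep the single-visit ANCOVA as a supportive analysis.

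The same section should state that the model relies on weights being missing at random given the weights and covariates in it, and how weights after death are handled.

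The cost is a few sentences and a standard procedure in the SAS or Stata already named in section 6; no new data are needed. The downside is the reliance on missing-at-random. If loss depends on weights that were never observed, the mixed model is biased too. A child with no post-baseline weight still contributes no outcome, so the comparison in 5.1 remains useful alongside it.
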